### Data collection, management, and monitoring

2.8

Baseline characteristic data will be collected, which consist of name, age, sex, employment, highest education level, diagnosis, typical symptoms, frequency of symptom occurrence, previous treatment, and family history. Outcomes will be assessed at baseline, 4 weeks after EA treatment onset, and 6-month follow-up. In each research center, original forms including case report forms and Adverse Events Form will be carefully checked and input into the computer. The trial will be monthly monitored by the Data and Safety Monitoring Board (DSMB) of 4 centers. The data manager of the DSMB from each center has the right to access the final data set and approve others’ requests of accessing the final data set.

### Statistical analysis

2.9

SPSS 24.0 (SPSS Inc., Chicago, IL) will be used to conduct the whole data analysis. The intention-to-treat (ITT) analysis will include any participant who has at least one treatment session. The “last observation carried forward” rule will be applied to manage missing data in ITT analysis of secondary outcomes, whereas the maximum likelihood estimation method will be used for primary outcome. Any participant who receives at least 9 treatment sessions during the trial will be included in per protocol analysis.

Considering the homogeneity of the baseline characteristics between groups, group *t* test for quantitative data and Chi test for qualitative data will be applied. Group *t* test for normally distributed data or Mann-Whitney *U* test for non-normally distributed data will be used to compare variables between groups. For differences within each group, repeated measured analysis of variance will be used to analyze assessments of different time points, whereas Wilcoxon signed-rank test will be selected for non-normally distributed data. A *P* value <.05 will be considered statistically significant (2-sided).

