#### Elimination criteria

2.2.4

Data from patients who meet any of the following criteria after treatment will be eliminated from the analyses of this trial: occurrence of severe AEs; aggravation of depression severity; poor compliance.

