#### Randomization and allocation

2.2.6

A computer program (Strategic Applications Software [SAS], version 9.1.3 [SAS Institute Inc., Cary, NC]) will be used by a statistician to generate the random allocation sequence. Four hospitals will be chosen as strata by using a stratified block randomization scheme. Opaque envelopes will be used to seal generated sequences and delivered to each center. Having enrolled participants meeting the selection criteria, the researcher will open the random allocation envelope in front of each participant one by one and assign him to 1 of 3 groups.

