### Blinding

2.3

This study will not be blinded.

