### Interventions

2.4

The enrolled participants will be allocated into 3 groups: electroacupuncture (EA) group, manual acupuncture (MA) group, or western medicine group.

Participants in EA group and MA group will receive 12 sessions of acupuncture treatment for 4 weeks, 3 times a week by experienced acupuncturists to ensure identical acupuncture treatment according to the standard operating procedures using stainless steel disposable needles (Energy, 40 mm in length and 0.25 mm in diameter, Jiajian Medical Supplies Co Ltd, Jiangsu, China). The same acupoints will be selected for participants in these 2 acupuncture groups. After skin sterilization, acupuncturists will puncture DU20, DU24, and GB8 horizontally 8 mm into the scalp skin. LR3, LI4, GB20, LI11, KI3, GB34, ST36 will be punctured vertically 15 mm into the skin, and only PC6 will be punctured 8 mm into the skin vertically to keep off the median forearm nerve. Needle manipulation including lifting, thrusting, and rotating will be done to obtain needling sensation (de-qi sensation). Acupoints of DU20, DU24, and bilateral ST36 will be stimulated using an electric current at a frequency of 2/15 Hz by EA device (Hwato, SDZ-II, Suzhou Medical Supplies Co Ltd, Jiangsu, China) in EA group, whereas EA device will not be used in MA group. The needle retention time for both two acupuncture groups will be 30 minutes for each session.

Participants allocated to western medicine group will only take 20 mg fluoxetine orally per day for 4 weeks instead of receiving acupuncture treatment.

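### The set labelled ITT drops randomised participants who leave after learning their arm but before first treatment, and neither session-based analysis set has a stated meaning for the fluoxetine arm

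*Protocol article*

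**What the plan says.** The protocol article (2.9 Statistical analysis) defines two analysis sets, both by counting sessions:

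- ITT: "The intention-to-treat (ITT) analysis will include any participant who has at least one treatment session".
- Per protocol: "Any participant who receives at least 9 treatment sessions during the trial will be included in per protocol analysis".

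Section 2.4 Interventions gives sessions to two arms only: "Participants in EA group and MA group will receive 12 sessions of acupuncture treatment for 4 weeks, 3 times a week". The third arm is described differently: "Participants allocated to western medicine group will only take 20 mg fluoxetine orally per day for 4 weeks instead of receiving acupuncture treatment".

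At allocation (2.2.6 Randomization and allocation), "the researcher will open the random allocation envelope in front of each participant one by one and assign him to 1 of 3 groups". Section 2.3 adds: "This study will not be blinded".

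Section 2.2.4 Elimination criteria adds a further exclusion. Data of participants who meet any of three conditions after treatment "will be eliminated from the analyses of this trial: occurrence of severe AEs; aggravation of depression severity; poor compliance". It does not say which analysis set this applies to.

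**The concern.** There are two separate faults.

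**The ITT label.** An intention-to-treat set holds everyone randomised, in the arm assigned. Requiring a first treatment makes it a modified set. Such a set can be defended when allocation is masked, because leaving before treatment then cannot depend on the arm. Here the participant knows the arm before treatment begins, so those who remain may no longer be comparable across arms, and the analysis would still be reported as ITT. The primary HAMD comparison would carry that selection.

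**The unit of the rules.** A session is a unit of acupuncture. The fluoxetine arm takes a daily oral drug, and the article states no equivalent. Someone applying the rules must therefore decide what qualifies a fluoxetine participant for either set. In an open trial, that decision could be made after results are visible.

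Both faults bear on the comparison with the only non-acupuncture control.

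**Working it through.** The plan gives no figure on this point to reproduce. The check applies the stated rules to each arm, then illustrates the possible bias.

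**1. Who leaves the ITT set.** The order of events is consent, envelope opened before the participant, then first treatment.
- Leaves after the envelope but before first treatment: randomised, aware of the arm, excluded.
- Leaves after one or more sessions: retained by the ITT rule, but still exposed to the elimination criteria in 2.2.4.

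The loss through the ITT rule is thus confined to the interval between allocation and first treatment.

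**2. How large that loss could be.** The documents give no rate for this interval. The 20% drop rate in 2.7 is overall, not by arm or timing. For illustration only, let *q* be the fraction of an arm leaving in the interval and *D* the difference in mean HAMD change between those who stay and those who leave. The mean over all randomised is (1 − *q*) × mean of stayers + *q* × mean of leavers, so using stayers alone shifts the arm mean by *q* × *D*.
- Arm size: 144/3 = 48. Section 2.7 also states 36 per group, which does not agree with 144 in three groups (36 × 3 = 108). The shift does not depend on arm size.
- *q* = 5%: 0.05 × 48 = 2.4 participants; *q* = 20%: 0.20 × 48 = 9.6 participants.
- Smallest shift: 0.05 × 2 = 0.1 points. Largest: 0.20 × 6 = 1.2 points.

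The ranges for *q* (5–20%) and *D* (2–6 points) are assumptions. If *q* × *D* is the same in two arms, the shifts cancel in their contrast. If leaving depends on the arm, they need not.

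**3. The rules applied to each arm.**

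| Arm | Planned treatment | At least 1 session | At least 9 sessions |
|---|---|---|---|
| EA | 12 sessions | applicable | 9/12 = 75% |
| MA | 12 sessions | applicable | 9/12 = 75% |
| Fluoxetine | daily for 4 weeks, 4 × 7 = 28 doses | no stated meaning | no stated meaning |

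For ITT, reading a session as any treatment gives the fluoxetine arm a workable rule, but only by supplying a definition the article lacks, and it leaves step 1 untouched. For per protocol, no reading settles the matter: no session equivalent is given, no visit schedule is stated that would yield nine contacts, and limiting the rule to acupuncture leaves the drug arm with no criterion. Section 2.10 Quality control names compliance with EA treatments only.

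**4. The elimination criteria.** As written, 2.2.4 removes data for severe adverse events, worsening depression or poor compliance from the trial's analyses without exempting ITT. Worsening depression is close to the primary outcome itself. Correcting the ITT sentence alone would leave this exclusion in force.

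**The case against.** The best defence is that acupuncture wording was carried over without an equivalent for the drug arm, and that a condensed article may leave drug-arm adherence to the full protocol or analysis plan. That is a fair account of how the per-protocol gap arose, and that set is supplementary. It does not help the ITT rule, which is a stated definition: a later plan must either inherit it or contradict it.

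It can also be said that immediate refusal should be uncommon. Section 2.2.3 excludes those unwilling to finish, and under 2.2.5 only participants who have signed consent are assigned. These steps reduce early leaving but do not prevent it. The Introduction cites a preference for complementary therapies among people with depression in two other countries and lists antidepressant side effects. That makes arm-dependent leaving plausible, without showing that it will occur here.

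A further fair objection is that participants with no post-baseline HAMD add almost nothing to a maximum likelihood comparison. Enlarging the set therefore helps little unless leavers are followed up. This stands, and the fix includes it.

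Three stronger readings are tempting, and the documents do not support them:
- *The whole fluoxetine arm is excluded.* This follows only from the most literal reading. The Discussion says the trial is designed to compare EA, MA and fluoxetine, and 2.9 plans between-group tests.
- *The control arm is held to a laxer standard, 9/28 = 32% against 75%.* This requires equating a session with a dose, which the article never does. It shows ambiguity, not a planned inequality.
- *Randomisation is undone, or a particular number of participants will be lost.* No early-leaving rate is given, and only those who leave before first treatment are affected by the rule.

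**Conclusion.** The ITT definition is wrong as written. In this open trial it removes randomised participants who leave between disclosure of the arm and first treatment, and the loss can differ by arm. The size is unknown from the documents; the 0.1–1.2 point shift in an arm mean rests wholly on assumed rates and differences. Separately, neither set has a stated meaning for the fluoxetine arm, and the control arm's per-protocol standard is undefined. The finding on the drug arm is an undefined criterion, not a plan to analyse no controls. The elimination criteria conflict with an ITT analysis as well and must be reconciled with it.

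**What to change.** - **ITT (2.9).** Define it as all randomised participants, analysed in the assigned arm, using the maximum likelihood method already chosen for the primary outcome.
- **Follow-up.** Continue to seek outcome assessments at the planned time points (4 weeks and 6 months) from participants who do not start or who stop treatment.
- **Elimination criteria (2.2.4).** State that eliminations for severe adverse events, aggravated depression or poor compliance do not apply to the ITT analysis.
- **Per protocol (2.9).** State adherence for each arm as a common fraction of assigned treatment. The existing threshold is 9/12 = 75% for EA and MA. The same fraction of the planned fluoxetine doses is 0.75 × 28 = 21. This defines an analysis set only and changes nothing in treatment.

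**Cost.** The text changes are a few sentences in 2.9 and 2.2.4. Fluoxetine intake must be recorded on the case report form, because the article mentions no drug counts. There will be slightly more missing data to handle. For secondary outcomes, the planned last-observation rule would carry baseline forward for anyone never reassessed, which is a further reason to follow up those who leave.

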#### Secondary outcomes

2.5.2

Secondary outcomes will be scored at the same time points as primary outcome, including Self-Rating Depression Scale (SDS), Depression Scale of traditional Chinese medicine (Depression Scale of TCM), brain fMRI, and blood biomarkers.

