### Sample size

2.7

The data statistician will be responsible for the calculation of the required sample size in each group. Based on previous studies, the cure effects of EA, MA and western medicine for depression were 15.7%, 17.4%, and 2.9%, respectively. Considering a significance level of 0.05 and a statistical power of 0.9, the calculated sample size in total is 120. Assuming about a 20% drop rate at a 1:1:1 allocation ratio, 144 participants will be recruited in this trial with 36 for each group.

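### Carrying the last observation forward for every secondary outcome, while HAMD uses maximum likelihood, can bias the arm comparisons in either direction or dilute a true difference

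*Protocol article*

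**What the plan says.** Section 2.9 (Statistical analysis) sets two rules for missing data. For the secondary outcomes, the LOCF "rule will be applied to manage missing data in ITT analysis of secondary outcomes". For HAMD the sentence continues "whereas the maximum likelihood estimation method will be used for primary outcome". No reason is given for the split.

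Three other statements determine what LOCF does in practice:

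- **Visits.** Section 2.8: "Outcomes will be assessed at baseline, 4 weeks after EA treatment onset, and 6-month follow-up". Section 2.5.2 gives the secondary outcomes the same schedule: "Secondary outcomes will be scored at the same time points as primary outcome". No visit lies between week 4 and 6 months.
- **Outcomes covered.** Section 2.5.2 lists the SDS together with "Depression Scale of traditional Chinese medicine (Depression Scale of TCM), brain fMRI, and blood biomarkers".
- **Who is imputed.** Section 2.9: "The intention-to-treat (ITT) analysis will include any participant who has at least one treatment session". One session is enough, so a patient with no post-baseline assessment can be in the analysis.

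The sample size section (2.7) anticipates loss: "Assuming about a 20% drop rate at a 1:1:1 allocation ratio". It gives no rate by arm.

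**The concern.** With three visits, LOCF has only two possible sources for a missing 6-month value: baseline, which means zero change by construction, or week 4, the end of treatment. Neither is an observation at 6 months. Copied values then enter the between-group and within-group tests of section 2.9 as if measured. For fMRI and serum markers, an earlier scan or assay stands in for one never taken.

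The size of the distortion depends on how many patients are lost in each arm and how far the mean moves after they leave. Section 2.3 states that the trial is unblinded, and section 2.4 compares 12 acupuncture sessions with a daily drug, so unequal drop-out is plausible, although the protocol does not predict it. Because the same patients' HAMD data follow a different rule, HAMD and SDS could disagree partly because of how missing values were handled.

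**Working it through.** **Inputs from the protocol article.** LOCF for secondary outcomes and maximum likelihood for HAMD (2.9); visits at baseline, week 4 and 6 months (2.8); about 20% drop-out, 144 recruited, 120 before the allowance (2.7). The plan gives no figure for the effect of LOCF, so there is none to reproduce.

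**Assumed inputs.** Drop-out of 15% vs 25% and 10% vs 30% in two arms (each averages 20%); a 10-point SDS improvement; for results in SD units, a 1 SD improvement by week 4.

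**1. Formula.** Let both arms follow the same true course, with fractions dA and dB lost at random. The false difference at 6 months (A minus B) is

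(dA − dB) × (mean at last observed visit − mean at 6 months).

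It is zero if dA = dB, or if the mean does not move after the last observed visit.

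**2. Loss before week 4 (baseline copied), 10-point improvement.** The LOCF mean change is (1 − d) × (−10).

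- 15% vs 25%: 0.85 × (−10) = −8.5 and 0.75 × (−10) = −7.5, a false difference of 1 point.
- 10% vs 30%: 0.90 × (−10) = −9 and 0.70 × (−10) = −7, a false difference of 2 points.

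**3. Loss after week 4 (week-4 value copied), mean moving a further 0.5 SD.**

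- 15% vs 25%: 0.10 × 0.5 = 0.05 SD.
- 10% vs 30%: 0.20 × 0.5 = 0.10 SD.

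The sign reverses according to whether patients go on improving or partly relapse.

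**4. Equal drop-out, true difference present.** Take true changes of −10 and −5, with 20% lost before week 4 in both arms. LOCF gives 0.8 × (−10) = −8 and 0.8 × (−5) = −4. The true difference of 5 becomes 4, a dilution of 20%.

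**5. Simulation under no true difference.** 48 per arm (144/3), SD 1, within-patient correlation 0.5, random drop-out, t test at 6 months, two-sided 0.05, 4,000 runs per scenario.

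| Loss | Course after week 4 | Drop-out | Bias (SD) | Type I error |
|---|---|---|---|---|
| Before week 4 | flat | 20% vs 20% | 0 | 5.2% |
| Before week 4 | flat | 15% vs 25% | 0.10 | 7.6% |
| Before week 4 | flat | 10% vs 30% | 0.20 | 14.3% |
| After week 4 | further 0.5 SD, either direction | 15% vs 25% | 0.05 | 5.6% to 6.1% |
| After week 4 | further 0.5 SD, either direction | 10% vs 30% | 0.10 | 7.0% to 8.1% |
| After week 4 | flat | 10% vs 30% | 0 | 4.5% |

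The simulation error on a 5% rate is √(0.05 × 0.95 / 4000) ≈ 0.34 percentage points, so 5.6% is not clearly above nominal.

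**6. Patients affected.** The protocol's own allowance is 144 − 120 = 24. Reading 20% as a share of those recruited gives 0.2 × 144 = 28.8, about 29. Both are upper figures: patients lost before any session leave the ITT set, and section 2.2.4 eliminates the data of some others.

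**The case against.** The strongest reply is that the harm is conditional and often small. Section 2.7 gives one overall drop-out rate. With equal drop-out and the same true course there is no false difference. With unequal loss after week 4 and a flat course there is none either. At 15% vs 25% with later loss, the type I error barely moves. The 10% vs 30% split is a threefold imbalance, and neither it nor the 10-point SDS change comes from the documents. All of this stands, and it limits the point to what LOCF can do.

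Three stronger readings are tempting but unsupported:

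- *LOCF will create false differences, or will favour a particular arm.* The protocol gives no arm-specific drop-out and no expected course after week 4, so neither the occurrence nor the direction can be inferred.
- *Single imputation also makes the tests too liberal in itself.* This was not shown. With equal 20% drop-out the simulated type I error stayed at about 5%; the inflation seen came from bias.
- *The remedy is to copy an existing HAMD mixed model.* Section 2.9 names a maximum-likelihood method but no such model. It then lists t tests, Mann-Whitney tests and repeated-measures analysis of variance.

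The per-protocol analysis (at least 9 sessions) removes many early drop-outs and so gives a partial check, but it is not a remedy for missing data. Finally, analysing fMRI on acquired scans only leaves two rules in the plan. That is fair, but an acquired-scan analysis does not count a copied scan as a measurement.

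**Conclusion.** The point holds as a conditional one. Section 2.9 fixes LOCF for all secondary outcomes, so this is a stated choice and not a detail left to an analysis plan. It can bias arm comparisons in either direction when drop-out differs between arms and the mean changes after the last observed visit. With equal loss before week 4 it dilutes a true difference in change in proportion to the loss.

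Under the assumed inputs the effect is modest: 1 or 2 SDS points for early loss, and 0.05 or 0.10 SD for later loss. It grows with the imbalance and with the size of the change. The carried-forward gap is about 5 months if the follow-up is counted from the start of treatment and 6 if from its end; the protocol does not say which. The primary HAMD analysis is not affected. Confidence is high that the rule is in the plan and that the mechanism works, but lower on how large the effect would be in this trial.

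**What to change.** In section 2.9, and in the SAP if there is one, delete LOCF. Analyse SDS, the TCM scale and the biomarkers (log-transformed where skewed) by maximum likelihood, as already chosen for HAMD. One way is a repeated-measures mixed model on all observed visits, with arm-by-visit contrasts at week 4 and 6 months replacing the t tests on filled-in data. Analyse fMRI on acquired scans only, and say so.

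The cost is small: no extra patients, visits or data, and somewhat more modelling work in the MIXED procedure of SPSS, the package already named. The text change goes slightly beyond the LOCF sentence, because the between-group tests for these outcomes change too. The price in assumptions is reliance on data being missing at random: expected bias is zero when drop-out is random or depends only on observed values, but not when it depends on unobserved ones.

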#### Primary outcome

2.5.1

The primary outcome of the clinical study will be the score changes of Hamilton Depression Scale (HAMD) between baseline, 4 weeks after EA treatment onset, and 6-month follow-up.

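### Arms are compared by unadjusted t or Mann-Whitney tests, to which the maximum likelihood handling stated for HAMD is not connected; one mixed model with baseline and hospital would repair this at almost no cost

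*Protocol article*

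**What the plan says.** All references are to the protocol article.

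- **Primary outcome (2.5.1):** the "score changes of Hamilton Depression Scale (HAMD) between baseline, 4 weeks after EA treatment onset, and 6-month follow-up".
- **Randomisation (2.2.6):** "Four hospitals will be chosen as strata by using a stratified block randomization scheme".
- **Between-arm comparison (2.9):** a group t test when data are normal; otherwise a Mann-Whitney U "test for non-normally distributed data will be used to compare variables between groups". No covariate or stratum term is mentioned.
- **Repeated measures (2.9):** "For differences within each group, repeated measured analysis of variance will be used to analyze assessments of different time points".
- **Missing data in the ITT analysis (2.9):** last observation carried forward for secondary outcomes, "whereas the maximum likelihood estimation method will be used for primary outcome".
- **Software (2.9):** SPSS 24.0 "will be used to conduct the whole data analysis".

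**The concern.** Two things do not fit together.

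First, the design collects baseline HAMD and balances the arms within hospital, but the named test makes limited use of the former and none of the latter. Subtracting baseline is not the same as adjusting for it. Leaving out a factor that randomisation has balanced makes the standard error somewhat too large.

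Second, maximum likelihood lets an incomplete record contribute only through a model for the repeated HAMD scores. A two-sample t or Mann-Whitney test contains no such model, and the one longitudinal analysis named is confined to changes within an arm, so it yields no treatment contrast. The missing-data method and the primary comparison are stated separately, and nothing joins them.

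At stake are some precision and, more importantly, the error rate of the primary comparison. That rate depends on how the gap is filled, and the article itself expects about 20% dropout (2.7).

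**Working it through.** **No figure in the plan to reproduce.** The sample size in 2.7 is built on cure rates. It gives no HAMD SD, no correlation between baseline and follow-up and no between-hospital variance. Those inputs are therefore assumptions below, shown as ranges.

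**Step 1: precision from baseline adjustment.** Let s be the follow-up SD, k the baseline SD divided by the follow-up SD, and rho the correlation between baseline and follow-up HAMD.

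- Change-score t test, variance per patient: s²(1 + k² − 2·rho·k)
- Adjusted for baseline as a covariate: s²(1 − rho²)
- Ratio, adjusted to change score: (1 − rho²)/(1 + k² − 2·rho·k)

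The two variances differ by s²(k − rho)². Adjustment therefore never loses in this formula, and it gains nothing when k equals rho.

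| rho | k = 1 | k = 0.7 | k = 0.6 |
|---|---|---|---|
| 0.3 | 0.91/1.40 = 0.65 | 0.91/1.07 = 0.85 | 0.91/1.00 = 0.91 |
| 0.5 | 0.75/1.00 = 0.75 | 0.75/0.79 = 0.95 | 0.75/0.76 = 0.99 |
| 0.6 | 0.64/0.80 = 0.80 | 0.64/0.65 = 0.98 | 0.64/0.64 = 1.00 |

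A value of k below 1 is plausible because 2.2.2 admits only patients with HAMD-17 above 17, which truncates the baseline distribution. Taking 48 per arm (144/3; section 2.7 also says 36, a separate discrepancy), the adjusted analysis would perform like a change-score t test with 48/0.65 = 74 per arm at one end and 48/1.00 = 48 at the other.

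**Step 2: hospital.** Omitting the stratification factor leaves the estimate unbiased and usually makes the test conservative. Without a between-hospital variance, the loss cannot be sized.

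**Step 3: the two ways to read the missing-data plan.** One pairwise comparison was simulated with no true effect: 48 per arm, 4 centres holding 5% of the variance, equal SDs, roughly 17-20% missing, 4000 runs. All of these parameters are assumptions.

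- *Reading A, patients with a missing value leave the test.* When dropout depended on baseline differently by arm, the change-score t test was biased by 0.20, 0.15 and 0.08 SD. Its type I error was 11.5%, 8.4% and 6.2% at rho 0.3, 0.5 and 0.7. Under completely random dropout it was unbiased, with type I error of about 4-5%.
- *Reading B, one EM-type imputation, then a t test.* This was unbiased, but type I error was about 9% (8-9% under completely random dropout), because imputed values are counted as observed and the standard error is too small.
- *Likelihood-type model with baseline and centre.* This was unbiased, with type I error of about 5%.

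**The case against.** The best case for the plan is that an unadjusted test on change scores is valid in a randomised trial, that omitting strata errs on the safe side, and that a condensed article may leave the exact likelihood model to a full protocol or SAP that is not shown. The first two points stand. The third stands for details such as covariance structure. It does not cover the main issue, because 2.9 positively names the between-arm tests and confines the repeated-measures model to within-arm differences.

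Four stronger readings are tempting, and the article does not support them.

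- *Baseline HAMD is ignored.* It is not: 2.5.1 defines the outcome as score changes, so baseline is subtracted. Only covariate adjustment is absent.
- *The maximum likelihood plan is unusable, so the analysis must be complete-case.* Nothing in 2.9 says that incomplete patients are dropped. EM imputation before a t test can be done; its fault is an understated standard error. Reading A is only one of two.
- *Precision improves by 20-35%.* That needs equal SDs at baseline and follow-up. With k of 0.6 to 0.7 the improvement is 0-15%.
- *Within-arm significance will be presented as efficacy.* Section 2.9 labels those tests as within-group and specifies between-group tests separately. Calling them descriptive is a sensible safeguard, not a correction of a stated claim.

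**Conclusion.** The point holds as an inconsistency in the stated analysis and as an improvement that costs almost nothing. The between-arm tests do not adjust for baseline HAMD or hospital, and the promised maximum likelihood handling has no between-arm model in which to operate.

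The variance reduction from baseline adjustment lies between near zero and about 35% for rho 0.3 to 0.6 and k 0.6 to 1. The documents do not narrow that range, and the contribution of hospital is unknown. The effect on type I error depends on how the gap is filled: about 9% with single imputation, and 6-12% with completers if dropout relates to baseline differently by arm, against a nominal 5%. These percentages belong to the simulated settings and are not predictions for this trial. The inconsistency itself does not rest on any of these assumptions.

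**What to change.** State one primary analysis for HAMD: a likelihood-based mixed model for repeated measures (SPSS MIXED) on change from baseline, with arm, visit, arm-by-visit, baseline HAMD, baseline-by-visit and hospital as fixed effects. Report adjusted pairwise differences between arms with 95% CIs at a primary time point named before analysis. Say that maximum likelihood handling of missing HAMD data means this model, and label the within-group tests as descriptive. For the primary outcome, this also removes the choice between a t and a Mann-Whitney test according to the shape of the data.

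The cost is a change of wording in the analysis section or SAP and a little more programming in the software already named. No extra patients, visits or measurements are needed.
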